# Investigating the effectiveness of care delivery at an acute geriatric community hospital for older adults in the Netherlands: a protocol for a prospective controlled observational study

**DOI:** 10.1136/bmjopen-2019-033802

**Published:** 2020-03-31

**Keywords:** geriatric medicine, older adults, community hospital, intermediate care facilities, readmissions, functional decline

## Abstract

**Introduction:**

Hospital admission in older adults with multiple chronic conditions is associated with unwanted outcomes like readmission, institutionalisation, functional decline and mortality. Providing acute care in the community and integrating effective components of care models might lead to a reduction in negative outcomes. Recently, the first geriatrician-led Acute Geriatric Community Hospital (AGCH) was introduced in the Netherlands. Care at the AGCH is focused on the treatment of acute diseases, comprehensive geriatric assessment, setting patient-led goals, early rehabilitation and streamlined transitions of care.

**Methods and analysis:**

This prospective cohort study will investigate the effectiveness of care delivery at the AGCH on patient outcomes by comparing AGCH patients to two historic cohorts of hospitalised patients. Propensity score matching will correct for potential population differences. The primary outcome is the 3-month unplanned readmission rate. Secondary outcomes include functional decline, institutionalisation, healthcare utilisation, occurrence of delirium or falls, health-related quality of life, mortality and patient satisfaction. Measurements will be conducted at admission, discharge and 1, 3 and 6 months after discharge. Furthermore, an economic evaluation and qualitative process evaluation to assess facilitators and barriers to implementation are planned.

**Ethics and dissemination:**

The study will be conducted according to the Declaration of Helsinki. The Medical Ethics Research Committee confirmed that the Medical Research Involving Human Subjects Act did not apply to this research project and official approval was not required. The findings of this study will be disseminated through public lectures, scientific conferences and journal publications. Furthermore, the findings of this study will aid in the implementation and financing of this concept (inter)nationally.

**Trial registration number:**

NL7896; Pre-results.

Strengths and limitations of this studyThis study will be the first to evaluate an acute geriatric community hospital in the Netherlands on both patient-reported and economic outcomes.Patients, informal caregivers and professionals were involved in the design and implementation of the Acute Geriatric Community Hospital.A process evaluation is planned to describe the experience of various stakeholders with this new concept and reveal barriers and facilitators to its implementation.A limitation of this study is the use of two historic cohorts as the control population, which may result in baseline differences between the control and intervention population.

## Introduction

### Background

Throughout the western world, there is an increase in older adults requiring acute care. Inpatient services are mostly consumed by those over the age of 65.^1 2^ The Netherlands, like many other countries, recently (2015) implemented stay-at-home policies leading to an increase in frail older persons living longer in the community.^3^ These reforms juxtaposed with an increased ageing population contribute to increased acute care utilisation.^4^ There has been a 19% increase in emergency department (ED) visits by Dutch older adults based on data from 2015 versus 2017.^5 6^

Many older adults come to the hospital with complex and atypical health problems.^5 7^ When older persons are subsequently hospitalised, health outcomes are known to be poor,^8^ particularly in patients with geriatric syndromes such as cognitive impairment or mobility impairment.^9 10^ For example, previous research showed that 30% of older persons gained new disabilities and 20% were readmitted within 30 days postdischarge.^11 12^ Hospitalisation itself may contribute to these poor outcomes, as hospitalised older adults often have reduced mobility because they are bedbound for approximately 20 hours a day.^13 14^ Low physical activity, in combination with poor nourishment and increased caloric demand due to acute illness, can lead to the loss of muscle mass and may contribute to the development of new disabilities, particularly in frail patients.^15 16^ Together with the noise in a hospital environment and the different personnel rotating between patient rooms, this contributes to sensory overstimulation and sleep deprivation, which may lead to confusion and the occurrence of delirium.^17–19^ Not only is the patient affected during hospitalisation but the informal caregivers also find hospital admissions stressful.^20^ Furthermore, previous research shows that a lack of discharge planning in the hospital can result in patients’ care needs being unmet.^21^ Hospital care as usual compared with discharge planning and follow-up show a higher rate of early readmissions.^22^ Readmissions can further affect patients’ recovery and increase healthcare costs.^23^

The complex medical needs of older persons, combined with their more dependent social situation, requires care delivery that offers guidance and support for realistic health and life goals.^24^ Perhaps a ‘gap’ exists between what care can be provided in an acute care hospital versus what can be provided in the community (primary care). Acute hospital care is secondary care with a focus on medical treatment and diagnostics, while primary care focuses on rehabilitation, nursing care and well-being.

Several alternative strategies to hospital admission and (nurse-led) intermediate care have been developed in the past as a substitute to conventional hospitalisation.^25^ Examples include (nurse-led) intermediate care and subacute geriatric care units, which are low-tech but with geriatric expertise.^26 27^ In general, these types of care have comparable outcomes to hospital care as usual. Moreover, nurse-led care in the USA, observation units and hospital at home care all show a cost reduction compared with care as usual.^25 26^ Until recently, the Netherlands had limited alternatives to hospitalisation for older persons who required acute care. Therefore, our research group sought to create an acute care alternative and opened the Acute Geriatric Community Care Hospital (AGCH) in July 2018, partnering with an academic hospital (Amsterdam UMC, location AMC), an insurance company (Zilveren Kruis) and a home care and nursing home agency (Cordaan). This acute geriatric care unit, which is based within an intermediate care facility, provides an alternative to conventional hospitalisation and delivers acute care closer to home.

The AGCH delivers acute care that is focused on early mobilisation and rehabilitation. Older persons with common medical problems (such as urinary tract infections, pneumonia or heart failure) and geriatric syndromes requiring hospital admission can be admitted to the AGCH. The AGCH provides a form of *intermediate* care between primary and secondary care. In the Netherlands, primary care includes general practice, community nursing and (temporary) admission to a nursing home. Secondary care includes specialist medical care and hospital admission. The care at the AGCH is supervised by a geriatrician and provided by nurses trained in geriatric care who have experience as either a hospital or community nurse. The single rooms are designed to accommodate respite for the informal caregivers. This concept of care is new to the Netherlands, and to our knowledge, there is only one comparable example in Europe: a ‘subacute care unit’ in intermediate care, which has been implemented in Spain.^27^

Our hypothesis is that with the provision of integrated medical and nursing care close to home, the AGCH is better suited to the needs of older adults with multiple chronic conditions and will lead to better patient health outcomes and reduced post-acute care costs. Therefore, this study is designed to compare care provided for older patients in the AGCH versus care provided in a hospital setting. Specifically, we aim to:

Evaluate the 90-day readmission rate of patients acutely admitted to the AGCH compared with a traditional hospital (usual care). Secondary outcomes include functional decline, institutionalisation, healthcare utilisation, the occurrence of geriatric syndromes such as delirium, health-related quality of life (HRQOL), mortality and patient satisfaction;Assess the cost-effectiveness of the AGCH versus usual care by performing an economic evaluation from a healthcare provider and societal perspective;Conduct a process evaluation using interviews with key stakeholders to identify facilitators and barriers to the implementation of the AGCH.

## Methods

### Setting

The AGCH opened in July 2018. It serves the south-eastern part of Amsterdam and its surrounding areas (an area with approximately 147 500 inhabitants).^28^ The AGCH is a 23-bed facility within a skilled nursing facility. The hospital has 24 hours geriatric and nursing assistance. Physiotherapy and routine laboratory testing are available during the workweek and simple X-ray is available once a week. The population that is eligible for admission to the AGCH are patients with a combination of an acute medical problem requiring hospitalisation (eg, pneumonia, exacerbation of heart failure or a urinary tract infection) and a geriatric condition (eg, delirium, cognitive impairment, falls, or functional impairment). Additionally, patients have to be haemodynamically stable and should not require complex diagnostic testing. In general, patients will not be admitted if they have the following exclusion criteria: (1) require care that can only be provided at an intensive care unit, (2) require surgery, (3) require urgent treatments or diagnostic tests that can only be provided in-hospital (eg, endoscopy, interventional radiology), (4) do not need hospital care but require transfer to a skilled nursing facility and (5) live in another region of the Netherlands.

Patients are directly admitted to the AGCH from the ED of the Amsterdam UMC-location Academic Medical Centre (AMC) in Amsterdam, which is a 1000-bed academic hospital with approximately 30 000 ED visits yearly. After the on-call geriatrician has assessed whether the patient is eligible for AGCH admission and the patient or representative has agreed to admission, the patient is transferred to the AGCH by ambulance. Since October 2019, patients can also be transferred from the EDs of other hospitals in Amsterdam. In the future, we plan to admit patients from home or general practice offices. Patients are admitted between 8.00 am and 23.00 pm, 7 days a week. At admission, a Comprehensive Geriatric Assessment (CGA) is conducted.^29^ The CGA gives an overview of all medical, functional, psychological and social problems. The CGA is discussed during multidisciplinary team meetings and used to formulate a care plan for each patient. For an overview of the admission process, the admission criteria and the components of this intervention, see figure 1.

**Figure 1 F1:**
[figure not shown]
Patient admission process and criteria, components of the AGCH intervention and goals. CGA, Comprehensive Geriatric Assessment^29^; GP, General practitioner.

### Study design

This study is a prospective, observational, cohort study with two historical control groups to evaluate the clinical and economic effects of the AGCH. The Strengthening the Reporting of Observational Studies in Epidemiology (STROBE) statement was used in preparing the study protocol (online supplementary appendix 1).^30^ Participants will be compared with hospital controls. The participants are recruited into the study and are assessed at admission, discharge, and 1, 3 and 6 months after discharge. Recruitment for this study started in February 2019. We plan to recruit for 18–24 months. The first 3 months of data collection consisted of a piloting phase to assess the feasibility of data collection and follow-up. In addition, a qualitative process evaluation on the facilitators and barriers to the implementation of the AGCH and patient experience will be conducted.

10.1136/bmjopen-2019-033802.supp1Supplementary data

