### Sample size calculation

In the Hospital-ADL study, 34% of participants experienced a readmission at 90 days.^35^ Assuming that 26% of patients admitted to the AGCH will experience a 90-day readmission, data from 515 patients at the AGCH will yield 80% power to detect an absolute difference of 8% in the readmission rate (which is a 25% reduction in the relative risk) using a two-sided test with an alpha of 0.05.^55^ As we expect 10% loss to follow-up, we aim to include a total of 567 (=515*1.10) patients from the AGCH.

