## Preliminary results

Between February 1st and December 20th, 2019, there were 362 consecutive admissions to the AGCH. Of these admissions, 26 were readmissions of patients who were already study participants. Of the remaining 336 admissions, 90 were by patients who did not meet the inclusion criteria. The remaining 246 patients or legal representatives and healthcare-proxy were approached for participation; 212 consented to participation (figure 2). The healthcare-proxy provided informed consent in 62 (29.2 %) of cases. Sixteen patients did not consent to follow-up by telephone but did consent to medical record review. The total study sample as of December 20th, 2019, consisted of 212 participants at baseline. Table 2 displays the baseline characteristics of this group. Participants had a mean age (SD) of 81.8 (8.4) years and 47.6% were male. Most participants were living independently before admission (81.1%). The most frequent admission diagnoses were infectious diseases (28.3%, mostly urinary tract infections), respiratory-related diseases (25.5%, of which half were pneumonia) and other (geriatric) diagnoses such as falls, delirium or sudden unexplained functional decline (25.1%). The main cardiovascular (9.4%) admission diagnosis was exacerbation of heart failure. The median (IQR) length of stay was 8.0 days (5.0–12.0) and 83.7% of patients were discharged to their original living situation.

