## Discussion

The complex acute medical needs of older patients require the delivery of specialised geriatric care. The traditional hospital environment may however not support recovery and maintaining independence. The AGCH aims to deliver care that focuses on medical treatment, early rehabilitation and proper transitions of care for older adults with multiple chronic conditions.^29 66^ The AGCH is unique in the Netherlands in its aim to combine multiple evidenced-based components of care for frail older persons at an alternative location for hospital care. The proposed research will provide insight into the clinical and economic effectiveness of care delivered at the AGCH, compared with hospital care.

Our preliminary results show that data collection at the AGCH is feasible and we expect to recruit enough patients to evaluate the primary outcome. There are also limitations to the design of this study. It is a non-randomised study and historic cohorts are used as control groups. Therefore, baseline differences between the intervention and control groups may hamper the matching between the groups. Additionally, the data from the historic cohorts were not collected in the same time period as the AGCH cohort. This is a limitation as work processes in hospitals may have changed over the years, which could influence our results. However, the two control populations do represent a geriatric population that was admitted for exacerbations of chronic conditions and acute illnesses that frequently occur in older persons. The strengths of the study are the involvement of patients and informal caregivers in the design of the concept of the AGCH. Moreover, a process evaluation will address the barriers and facilitators to implementation of the AGCH in the Dutch Healthcare system. In short, this research will provide valuable insights into the implementation of this concept of care in other regions of the Netherlands and abroad.

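### At the reported accrual of 20 per month, the 18–24 month recruitment window yields about 360–480 AGCH patients, not the stated 567

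*Protocol article*

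**What the plan says.** Four parts of the protocol article bear on this.

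- **Study design:** recruitment began in February 2019, and "We plan to recruit for 18–24 months". The first 3 months were a pilot of data collection and follow-up.
- **Sample size calculation:** "data from 515 patients at the AGCH will yield 80% power to detect an absolute difference of 8% in the readmission rate", and after an allowance for 10% loss to follow-up, "we aim to include a total of 567".
- **Preliminary results:** from 1 February to 20 December 2019 there were 362 AGCH admissions. After repeat admissions and ineligible patients were removed, 246 patients or their representatives were approached and "212 consented to participation".
- **Discussion:** in the same sentence that cites the preliminary results as showing feasibility, "we expect to recruit enough patients to evaluate the primary outcome".

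Setting adds that other Amsterdam emergency departments could refer patients from October 2019, and that admission from home or general practice is planned, without a date or an expected volume.

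**The concern.** The article prints a recruitment period, a target, an interim count and an assurance about recruitment, so a reader can test them against each other. Projected forward, the interim count does not reach the target within the period, yet the assurance is offered alongside that count. No accrual projection is given, and neither the period nor the target is adjusted.

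At stake is the precision of the primary comparison. If recruitment ended with the stated period at the observed rate, fewer AGCH patients would be analysed than the calculation calls for. A null result on 3-month readmission could then be read as coming from a study of the stated size.

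**Working it through.** **1. The plan's own sample size.** Inputs from the Sample size calculation: control rate 34%, AGCH rate 26%, "using a two-sided test with an alpha of 0.05", 80% power. No allocation ratio is stated. With equal groups and a pooled-variance test of two proportions:

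- Null standard error: √(2 × 0.30 × 0.70 / 515) = 0.02856
- Alternative standard error: √((0.34 × 0.66 + 0.26 × 0.74) / 515) = 0.02845
- Power: Φ((0.08 − 1.96 × 0.02856) / 0.02845) = Φ(0.845) = 0.801

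So 515 reproduces on a 1:1 basis, and 515 × 1.10 = 566.5, rounded up to 567. There is no error in these figures. The 1:1 ratio is inferred from the match.

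**2. Observed accrual** (Preliminary results). 1 February to 20 December 2019 is 323 days; 323 / 30.4375 = 10.61 months.

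- Enrolled: 212 / 10.61 = 19.98 per month
- Approached: 246 / 10.61 = 23.2 per month
- All admissions: 362 / 10.61 = 34.1 per month

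The 212 include 16 patients who declined telephone follow-up but allowed record review; they are counted here.

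**3. Projection at that rate.**

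- 18 months: 19.98 × 18 = 360, which is 207 short (63% of target)
- 24 months: 19.98 × 24 = 479.5, about 480, which is 87 short (85% of target)
- Time to 567: 567 / 19.98 = 28.4 months
- Time to 515 with no loss at all: 515 / 19.98 = 25.8 months

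**4. Rate needed after 20 December 2019.** 567 − 212 = 355 still to recruit.

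- By month 24: 355 / (24 − 10.61) = 26.5 per month, 1.33 times observed
- By month 18: 355 / (18 − 10.61) = 48 per month, 2.4 times observed and above the 34 per month of all admissions

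**5. Sensitivity of the 24-month total.**

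- Chance variation: the 95% Poisson range for the rate is 17.4–22.9 per month. With 212 + rate × 13.39, this gives 445–518.
- Every approached patient consenting throughout: 23.2 × 24 ≈ 556.
- Slow pilot (assumption, as no monthly counts are given): if the first 3 months ran at 5, 10 or 15 per month, the later rate is (212 − 3 × pilot rate) / 7.61, or 25.9, 23.9 or 21.9 per month. The 24-month totals are 558, 532 and 506; the 18-month totals are 403, 389 and 374.

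None of these reaches 567.

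**6. Power if the window is kept at the observed rate.** Same rates and test, with 90% of those enrolled analysed (360 × 0.9 = 324; 480 × 0.9 = 432):

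| Comparator | 324 AGCH (18 months) | 432 AGCH (24 months) |
|---|---|---|
| Equal number of controls (inferred basis) | 60% | 73% |
| 401 controls (Hospital-ADL cohort) | 65% | 71% |
| 1075 controls (674 + 401), unweighted | 78% | 86% |

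Propensity weighting would ordinarily lower these figures; the article gives nothing from which to size that loss.

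**The case against.** A reader might infer that the window, the target and the 80% power cannot all be true. The documents do not support that. A rate of 26.5 per month from late December 2019 reaches 567 at month 24, inside the stated window, and the article gives reasons why accrual might rise. Other emergency departments had been referring for at most 81 of the 323 days (1 October to 20 December), so the average mostly reflects one referring department. Admission from home and general practice was still to come, and the pilot may have pulled the average down. Without monthly counts, a rise already under way cannot be excluded. As an illustration, 17.8 per month for the 242 days before October and 26.5 per month for the 81 days after gives 17.8 × 7.95 + 26.5 × 2.66 = 212. Beds do not appear to bind either: 34 admissions a month at the median stay of 8 days occupy about 34 × 8 / 30.4 ≈ 9 of the 23 beds, using the median as a rough proxy.

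A reader might also infer that the Discussion promises 567 patients by a set date, or that the study is bound to be underpowered. The Discussion states an expectation and names neither number nor date. No rule says recruitment stops when the window closes. Against both cohorts combined, unweighted power at 24 months is 86%.

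All of this stands, and it limits the point to a projection at the observed rate. It does not remove the point. The article does not quantify a rise in accrual or invoke one to support its expectation. The wider referral is already partly in the observed rate. The only size it calls for is 567, and the calculation does not say that it relies on 1075 controls. None of these arguments makes the 18-month end reachable. Nor is this a detail merely left to a fuller document, since the article itself prints the figures that do not fit.

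**Conclusion.** The point holds as a mismatch at the study's own observed rate. The stated window gives 63–85% of the stated target, and the preliminary results do not by themselves support the expectation of sufficient recruitment. The 24-month end is possible only if accrual rises by about a third and stays there; whether wider referral would do this cannot be told from the article. The 18-month end is not realistic.

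The conclusion assumes that the average rate up to 20 December 2019 continues. The consequence for power depends on the comparator: on the 1:1 basis, or against the 401 controls alone, it is clearly below 80% throughout the window. Against all 1075 controls it runs from just under to somewhat above 80% before weighting. This is a correctable inconsistency in the planning figures and does not undermine the design.

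**What to change.** **Preferred:** define the end of recruitment as reaching the stated target of 567, and drop the 18-month end. At the present rate this means about 28–29 months from February 2019, that is, to about June 2021, with the 6-month follow-up ending about December 2021. That still fits the Economic evaluation section, which allows 2021 as the final year of data collection.

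**If 24 months is a fixed limit:** state the rise in accrual that is assumed and its source. Restate the expected enrolment at the present rate (about 480, about 432 evaluable) with its power: about 73% on a 1:1 basis, 71% against 401 controls, and 86% against 1075 controls before the loss from propensity weighting. Say which comparator the calculation uses.

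In either case, reword the Discussion sentence so that the expectation rests on the projection chosen.

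**Cost:** a recruitment period about 4–5 months longer than the upper end now stated, with no more patients than already planned; or, under the second option, a less favourable stated power. Otherwise the change is one of wording.
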